### Table 1 Inclusion and exclusion criteria

| **Subject eligibility** | |
| --- | --- |
| **Inclusion**  **criteria**  **Exclusion criteria** | 1. Met the criteria for a DSM-5 diagnosis of depression without psychotic features; 2. MADRS scores ≥ 12; 3. Inpatients aged 12–17 years; 4. Participants with intelligence level in the normal range, normal perception, self-expression ability, and who can complete the baseline scale assessment; 5. Informed consent signed by the participants and their legal guardians. 6. Participants with a DSM-5 diagnosis of other mental disorders, including addictive disorders, developmental disorders, bipolar disorder, substance-related disorders, and schizophrenia (except anxiety disorders); 7. Participants with severely disruptive or aggressive behaviors, or positive suicidal ideation (suicide item scores of the MADRS > 4); 8. Participants with severe psychotic symptoms (presence of pain or common hallucinations and/or delusions); 9. Participants with clinically significant and uncontrolled pulmonary, endocrine, immunological, cardiovascular diseases (based on ancillary examination, physical examination, medical history); 10. According to the research group, participants who could not cooperate with the cognitive function tests or would not be suitable for this study. |

**Abbreviations**: ***DSM-5***: Diagnostic and Statistical Manual of Mental Disorders; ***MADRS***: Montgomery-Asberg Depression Rating Scale.

## Randomization

Random sequences will be generated by a specially recruited staff member, who will use the SPSS Rv.Uniform function to generate a random number table. The random seed parameters and groupings will be sealed as confidential data in an opaque envelope. The random sequence and grouping data will be kept by one designated person, who will open the envelope after the subjects meeting the criteria are selected to enter the study and have signed the informed consent form. The investigator will be informed regarding the participants’ treatment allocation, and the participants will be randomized according to a pre-defined randomization protocol.

## Blinding

This study will use a single-blind approach because in this intervention, the participants and health care professionals cannot be blinded to the study conditions. Therefore, to minimize the impact of information bias, the researcher administering the outcome measurement will be unaware of the group assignment. To maintain researcher blindness regarding group assignment, the same researcher will not conduct follow-up measurements on the same pair of elements.

## Intervention

All interventions will be conducted in a group format and delivered by experienced psychotherapists. All participants will use electronic exercise wristbands (Beijing Xiaomi Technology Co., LTD., [Product number](javascript:;): Xiaomi Band 7pro, M2140B1) to record the daily intensity of their physical activities. The electronic exercise wristbands utilize photocapacitance pulse wave tracing (PPG) and acceleration sensors to measure the intensity of physical activity in adolescents[34-37]. During the study period, the participants will only receive conventional clinical medication and care, and will not be involved in any other psychological therapy programs.

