## Intervention group: BAPT

The intervention group will receive 9 BAPT sessions, twice a week, for 60 minutes each time. Each session will consist of BA (30 minutes) and GPA (30 minutes). The BA procedure was adapted from the protocols of Kellett et al.[38] and Lejuez et al.[39], with appropriate modifications according to the actual situation. In the BA sessions, participants will receive information about the core principles of BA, which can be summarized as nine topics as follows: (1) Initiation of BA: the sense of values and connection; (2) the BA model and emotional monitoring; (3) getting motivated: goal-oriented behavior; (4) getting activated: situation-action-emotion; (5) problem solving skills; (6) goal setting and adjustment; (7) identifying obstacles and overcoming avoidance; (8) thinking: worrying, ruminating; (9) prevention of recurrence. Each session will contain one topic, and the GPA associated with that topic will be completed after that part of the BA. The BAPT scheme is shown in **Table 2**. All GPAs were designed or modified by the research team to be competitive, adventurous, interactive, and to follow certain rules that are in line with the physical and mental development characteristics of adolescents[26]. For example, “Cat catches mouse” is a type of exciting chase game in which participants are asked to choose one of three roles: one pair of participants are the cat and mouse, while the others are fences. All of the fences form a circle such that the participants are standing about 1 meter apart. The mouse is inside the circle and the cat is outside, and when the game starts, the cat attempts to enter the circle to catch the mouse. To avoid being captured, the mouse can choose a fence by touching that participant. Then, the original fence becomes the cat, the original cat becomes a mouse, and the cycle continues until the cat catches the mouse. The game is interesting and challenging because of the constantly changing roles of the participants in the game. The researchers rated all GPAs as moderate to high intensity physical activity after testing with electronic exercise wristbands. Therefore, we have mapped out a complete risk prevention scenario designed to protect the safety of the participants. If an adverse event occurs, it will be recorded and reported to the Ethics Committee.

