## Control group: BA

The control group intervention will be same as the BA in the intervention group, but without the GPA. Each session will be 60 minutes long because of the extended discussion. Homework will be the same as in the intervention group, but without the socio-motor game suggestions.

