## Statistical analysis

### Sample size calculation

The depressive symptom scores of the study subjects will be used as the main outcome index, with a bilateral α = 0.05 and a 90% confidence interval. In a previous study on the effects of BA combined with traditional exercise therapy, the depression scores of the intervention group at the baseline and at the 16-week follow-up period were 27.3 ± 8.0 and 16.0 ± 9.5, respectively[46]. Therefore, we expect that the depression score of the experimental group in the present study could be decreased by 11.3 points compared with the baseline and 4.8 points compared with the control group. We used PASS 15 software to calculate the sample size of the experimental group: N1 = N2 = 84. Considering the expectation that 10%­–20% of the cases will be

lost during the period following the study, the number of participants needed in the intervention group and control group will be about 100, respectively.

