## Data analysis

The study is based on the intention-to-treat principle. SPSS 28.0 will be used for data analysis. First, to ensure comparability after randomization, we will compare the differences between the groups at the baseline. The continuous variables will be analyzed by a t-test when the data have a normal distribution, and non-normally distributed data will be analyzed using the Mann-Whitney U test. Baseline differences between groups in terms of sociodemographic and clinical variables will be assessed using Chi-square tests for categorical variables and an analysis of variance (ANOVA) for continuous data. To compare intervention effects, a mixed-effect regression model will be used. Group (BAPT or BA) will be used as an inter-subject factor, and time (baseline, post-treatment, and follow-up) as an intra-subject factor. We will utilize Cohen's d to achieve both the intra- and intergroup analyses. P < 0.05 was set as statistically significant.

Financial Support

This study was supported by Science and Technology Program of Guangzhou (grant No. 205171098044), Guangzhou Municipal Key Discipline in Medicine (2021-2023), Guangzhou High-level Clinical Key Specialty, and Guangzhou Research-oriented Hospital.

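### Both arms are treated in therapy groups, but the sample size makes no allowance for within-group correlation and the described model names only arm and time

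*Protocol*

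**What the plan says.** **Delivery.** The Protocol's Intervention section says of both arms: "All interventions will be conducted in a group format and delivered by experienced psychotherapists". Under Intervention group: BAPT, the physical games depend on participants playing with and against each other: "All GPAs were designed or modified by the research team to be competitive, adventurous, interactive". Under Control group: BA, the content is the BA part alone, and "Each session will be 60 minutes long because of the extended discussion". Each arm has nine sessions. Under Randomization, the allocation envelope is opened once eligible participants have consented, so participants and not therapy groups are randomised.

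**Sample size.** The Sample size calculation section sets the error rates "with a bilateral α = 0.05 and a 90% confidence interval". It cites depression scores from an earlier study at baseline and week 16 that "were 27.3 ± 8.0 and 16.0 ± 9.5, respectively[46", and expects a benefit of "4.8 points compared with the control group". It concludes: "We used PASS 15 software to calculate the sample size of the experimental group: N1 = N2 = 84". Allowing for 10% to 20% loss, this becomes about 100 per arm. No therapy-group size, ICC or design effect appears.

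**Model.** Data analysis plans a mixed-effect regression in which "Group (BAPT or BA) will be used as an inter-subject factor, and time (baseline, post-treatment, and follow-up) as an intra-subject factor". Here the word group means treatment arm. Neither therapy group nor therapist is mentioned.

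**The concern.** This is individual randomisation followed by group treatment. Members of one therapy group share a therapist, the same peers and the same session dynamics, so their MADRS scores can be expected to resemble each other more than scores from different groups. A mixed model with arm, time and a participant effect handles repeated measurements on one person. It does not handle correlation between different people in the same group.

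Two consequences follow if that correlation is positive. First, the variance of the arm difference is larger than a model without a therapy-group term reports, so the primary comparison rejects too often. Second, the information in 84 participants per arm is less than the sample size calculation assumes. The comparison affected is the primary one, BAPT against BA on MADRS, where an understated standard error could support a false claim of superiority.

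**Working it through.** **Step 1. Reproduce the planned N.** Inputs from Sample size calculation: difference 4.8, week-16 SD 9.5, two-sided alpha 0.05, equal arms. The 90% is labelled a confidence interval; it is tried here as power. With independent participants, the standard error at 84 per arm is 9.5 × √(2/84) = 1.466, and the noncentrality is 4.8/1.466 = 3.27 on 166 df.

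- 83 per arm: power 89.9%
- 84 per arm: power 90.2%

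So 84 is the smallest N reaching 90% under independence. Alternatives do not give 84: SD 8.0 gives 60, and 80% power with SD 9.5 gives 63. Enrolment also fits: 84/(1 − 0.16) = 100.

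**Step 2. Inputs the Protocol does not give.** Therapy-group size m and ICC are assumed: m = 6 to 10, ICC = 0.01 to 0.05, the same in both arms.

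**Step 3. Formulas.**

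- Design effect: DE = 1 + (m − 1) × ICC
- Real type I error of a naive 5% test: 2 × [1 − Φ(1.96/√DE)]
- Power: noncentral t with noncentrality 4.8/(9.5 × √(2 × DE/n)), on 2n − 2 df (individual level, optimistic) or 2 × (n/m) − 2 df (cluster level, pessimistic)

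Example, m = 8 and ICC 0.05: DE = 1 + 7 × 0.05 = 1.35; type I error = 2 × [1 − Φ(1.96/1.162)] = 9.2%; noncentrality = 3.27/1.162 = 2.82, giving 80.0% power on 166 df.

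**Step 4. Results at 84 evaluable per arm.**

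| m | ICC | DE | Naive type I error | Power, individual df | Power, cluster df |
|---|---|---|---|---|---|
| 6 | 0.01 | 1.05 | 5.6% | 88.8% | 86.8% |
| 6 | 0.02 | 1.10 | 6.2% | 87.4% | 85.2% |
| 8 | 0.05 | 1.35 | 9.2% | 80.0% | 76.2% |
| 10 | 0.05 | 1.45 | 10.4% | 77.1% | 71.9% |

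**Step 5. Vary the number of completers** (individual-level df), using the Protocol's own loss range from 100 enrolled.

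| Completers per arm | Independent | m = 6, ICC 0.01 | m = 8, ICC 0.05 | m = 10, ICC 0.05 |
|---|---|---|---|---|
| 90 (10% loss) | 92.1% | 90.8% | 82.7% | 79.9% |
| 80 (20% loss) | 88.8% | 87.3% | 78.0% | 75.1% |

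With 90 completers, 90% power survives a design effect of about 1.07 (90.3% at m = 8, ICC 0.01). With 84, the margin is only 0.2 percentage points.

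**The case against.** **The model may be completed elsewhere.** Data analysis names two factors and no random effects at all, not even a participant intercept. Random-effects structure and degrees of freedom are often left to the statistical analysis plan, which is not at hand. This stands in part: a reader might infer that the trial has decided to analyse participants as independent, and the Protocol does not say so. It does fix the sample size without clustering, and a later plan can use therapy group only if membership was recorded.

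**The shortfall is not established.** A reader might infer that power is certainly below 90% and the standard errors certainly too small. The documents do not support that. Group size and ICC are unknown, the 90% is inferred to be power, and with 90 completers and a small design effect the target is still met. Also, 84 rests on an unadjusted endpoint SD. If the model uses baseline efficiently, a baseline-endpoint correlation r offsets a design effect when DE × (1 − r²) = 1, that is r = 0.30 for DE 1.10 and r = 0.51 for DE 1.35. That correlation is not in the documents either. Such a gain could restore power, but it would not correct the type I error of a model that ignores therapy group.

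**The sizes shown may be pessimistic.** Cluster-level df is the harshest choice, and dropout also shrinks the groups. If 10 per group falls to 8.4, DE at ICC 0.05 is 1 + 7.4 × 0.05 = 1.37 and power at 84 is 79.4%, not 77.1%. This stands, and is why ranges are given.

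**A single group identifier may not exist.** The Protocol does not say whether groups are closed or rolling, and sessions 5 to 9 follow discharge. It also does not say whether therapists work in one arm or both. This stands and shapes the fix.

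**Conclusion.** The point holds in conditional form. Both arms are treated in groups; the sample size is exactly the independent-participant figure with almost no slack; and the model as described has no term for therapy group. If the ICC is positive and the model is run as described, the primary test is anti-conservative. Power at 84 evaluable per arm then falls below the inferred 90%, except at a negligible ICC.

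Under the assumed range (6 to 10 members, ICC 0.01 to 0.05), the naive type I error is about 5.6% to 10.4%. Power at 84 per arm is about 89% to 77% with individual-level df, or 87% to 72% with cluster-level df. It is about 91% to 80% with 90 completers and 87% to 75% with 80 (individual-level df). The direction follows from the design; the size depends on the assumed values. The sample size is the firmest part, because the Protocol itself fixes it.

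**What to change.** 1. Record therapy-group membership and therapist prospectively on the CRF, session by session if membership can change.
2. Include a therapy-group random effect in both arms of the primary mixed model, with small-sample degrees of freedom (Satterthwaite type). If groups are rolling or are re-formed after discharge, use a multiple-membership or session-block version. State whether therapists are nested in arm or work across arms.
3. Restate the power for about 100 enrolled per arm over a stated range of group size and ICC, and label the 90% as power if that is what was meant.

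The cost is a small addition to the CRF, one extra model term, and a less favourable stated power. No additional patients are asked for, so this corrects the test and makes the power statement honest; it does not restore 90% power.

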## Intervention group: BAPT

The intervention group will receive 9 BAPT sessions, twice a week, for 60 minutes each time. Each session will consist of BA (30 minutes) and GPA (30 minutes). The BA procedure was adapted from the protocols of Kellett et al.[38] and Lejuez et al.[39], with appropriate modifications according to the actual situation. In the BA sessions, participants will receive information about the core principles of BA, which can be summarized as nine topics as follows: (1) Initiation of BA: the sense of values and connection; (2) the BA model and emotional monitoring; (3) getting motivated: goal-oriented behavior; (4) getting activated: situation-action-emotion; (5) problem solving skills; (6) goal setting and adjustment; (7) identifying obstacles and overcoming avoidance; (8) thinking: worrying, ruminating; (9) prevention of recurrence. Each session will contain one topic, and the GPA associated with that topic will be completed after that part of the BA. The BAPT scheme is shown in **Table 2**. All GPAs were designed or modified by the research team to be competitive, adventurous, interactive, and to follow certain rules that are in line with the physical and mental development characteristics of adolescents[26]. For example, “Cat catches mouse” is a type of exciting chase game in which participants are asked to choose one of three roles: one pair of participants are the cat and mouse, while the others are fences. All of the fences form a circle such that the participants are standing about 1 meter apart. The mouse is inside the circle and the cat is outside, and when the game starts, the cat attempts to enter the circle to catch the mouse. To avoid being captured, the mouse can choose a fence by touching that participant. Then, the original fence becomes the cat, the original cat becomes a mouse, and the cycle continues until the cat catches the mouse. The game is interesting and challenging because of the constantly changing roles of the participants in the game. The researchers rated all GPAs as moderate to high intensity physical activity after testing with electronic exercise wristbands. Therefore, we have mapped out a complete risk prevention scenario designed to protect the safety of the participants. If an adverse event occurs, it will be recorded and reported to the Ethics Committee.

After each session, the participants will receive homework, where they will be encouraged to schedule activities (socio-motor game, etc.) that feel enjoyable, rewarding, and offer a sense of control during the following week, and to monitor the impact of these activities on their personal mood. Homework will be collected by the researchers once a week.

### Table 2 The scheme of the BAPT

| Time | Session | Course theory | Game-type physical activity |
| --- | --- | --- | --- |
| Weeks 1 - 2  (During hospitalization) | 1 | Initiate BA: the sense of values and connection | Strong Winds Blow |
|  | 2 | The BA model and emotional monitoring | Balloon Missile |
|  | 3 | Get motivated: goal-oriented behavior | Giant's Hat |
|  | 4 | Get activated: situation-action-emotion | Overcome The Obstacle |
| Weeks 3 - 4  (Returning to the  department after  discharge) | 5 | Problem solving skills | Transmitting Things By Sole |
|  | 6 | Goal setting and adjustment | Blindfolded Communication |
|  | 7 | Identify obstacles and overcome avoidance | Cat Catches Mouse |
|  | 8 | Thinking: worrying, ruminating | Knee Pat |
|  | 9 | Prevention of recurrence | Queen Ant Game |

**Abbreviations:** Weeks 1–2: complete sessions 1–4; Weeks 3–4: complete sessions 5–9.

## Control group: BA

The control group intervention will be same as the BA in the intervention group, but without the GPA. Each session will be 60 minutes long because of the extended discussion. Homework will be the same as in the intervention group, but without the socio-motor game suggestions.

## Intervention Fidelity

The BA or BAPT interventions will be delivered by psychotherapists recruited from the clinical staff of the Affiliated Brain Hospital of Guangzhou Medical University. All psychotherapists will complete a two-week consistency training program. Group supervision will be conducted by a senior clinical psychologist throughout the study, and all sessions will be recorded so that the treatment adherence can be assessed.

## Safety and monitoring

Before each intervention session, the subjects will complete the 10th item of the clinician-rated Montgomery-Asberg Depression Rating Scale (MADRS) for suicidal risk. If the scores are > 4, the subjects will be temporarily withdrawn from the study. During the intervention, if the subjects show severe self-injury or suicidal behavior, they also will be temporarily withdrawn from the study. Subsequently, the doctors in the project team will conduct suicide crisis interventions and follow-up visits, and then organize expert discussions regarding any incidents to avoid recurrence.

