Participants aged 12 to 17 years will be eligible if they are defined as having depression by using DSM-5, but if they meet one of the following exclusion criteria they will not be allowed to take part: (1) Participants with a DSM-5 diagnosis of other mental disorders, including addictive disorders, developmental disorders, bipolar disorder, substance-related disorders, and schizophrenia (except anxiety disorders); (2) Participants with severely disruptive or aggressive behaviors, or positive suicidal ideation (suicide item scores of the MADRS > 4); (3) Participants with severe psychotic symptoms (presence of pain or common hallucinations and/or delusions); (4) Participants with clinically significant and uncontrolled pulmonary, endocrine, immunological, cardiovascular diseases (based on ancillary examination, physical examination, medical history); (5) According to the research group, participants who could not cooperate with the cognitive function tests or would not be suitable for this study.

Prior to participation in this study, all subjects and their legal guardians must be fully informed about the project and sign a written informed consent form. The participants will be divided into intervention group and control group according to a pre-defined randomization protocol. The intervention and control groups received 4 weeks of BAPT and 4 weeks of BA respectively. Participants in both groups will be treated and cared for according to the same criteria, but will not be involved in any other psychological therapy programs.

Therapeutic effect evaluation will be done at the baseline, week 2 (the end of the basic intervention), week 4 (the end of all the high-order intervention), week 8, and week 16 by the MADRS, BDI-II-C, BADS-SF, ANSAQ, ISI, IPAQ-SF, and Likert Scale. The primary outcome was whether BAPT could decrease depressive symptoms in adolescents by MADRS scores.

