# Methods and design

## Study design and setting

This study is a two-arm single-blind RCT. The intervention and control groups will receive 9 sessions of BAPT and 9 sessions of BA, respectively. Because adolescents with depression who are hospitalized generally have a relatively short stay in the hospital, the participants in this study will complete the first 4 sessions during hospitalization and then will be asked to return to the department for the remaining 5 sessions after they are discharged.

This study was approved by the ethics committee of the Affiliated Brain Hospital of Guangzhou Medical University on April 27, 2023 (Ethics number: 2023 [027]) and registered with the China Clinical Trials Center under the registration number ChiCTR2300072671. The design of this protocol is in line with the Standard Protocol Items: Recommendations for Intervention Trials (SPIRIT). **Fig. 1** presents the enrolment, intervention and evaluation schedule for SPIRIT. **Fig. 2** presents a flow chart of the study. The study will be supervised by the Department of Child and Adolescent Psychiatry (DCAP) and the Academic Management Committee of the Affiliated Brain Hospital of Guangzhou Medical University.

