
At the baseline, week 2 (the end of the basic intervention), week 4 (the end of all the high-order intervention), week 8, and week 16, participants from the two groups will be evaluated with the corresponding scales to assess the degree of depression, behavioral activation level, non-suicidal self-injury behavior, and sleep quality scores. We will also calculate the improvement of symptoms for each dimension in each group at each time point, and then compare the divergences between the two groups. All participants will receive an electronic exercise wristband as a reward after they completed the follow-up.

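### The written response to suicidality covers only the session period (weeks 1–4), and its action is worded as withdrawal from the study, not from the sessions

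*Protocol*

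**What the plan says.** Safety and monitoring sets two triggers.

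- The first is item 10 of the MADRS, rated ahead of every session: "If the scores are > 4, the subjects will be temporarily withdrawn from the study".
- The second is conduct and not a score, and it leads to the same action: "During the intervention, if the subjects show severe self-injury or suicidal behavior, they also will be temporarily withdrawn from the study".

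After either trigger, the project team's doctors provide crisis care and clinical follow-up, and experts discuss the incident. The section gives no criterion for return, does not say who decides on it, and does not mention the scheduled outcome visits.

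The other relevant provisions are these:

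- **Entry.** Table 1 excludes subjects with "positive suicidal ideation (suicide item scores of the MADRS > 4", the same cut-off.
- **Sessions.** Under Study design and setting, participants have the first four sessions as inpatients and "then will be asked to return to the department for the remaining 5 sessions after they are discharged". Table 2 has weeks 3–4 "complete sessions 5–9", so the last session falls in week 4.
- **Outcome visits.** The Synopsis schedules assessment at baseline, week 2, week 4, "week 8, and week 16 by the MADRS" and other scales, among them the self-injury questionnaire. Efficacy evaluations says that at these visits "participants from the two groups will be evaluated with the corresponding scales to assess the degree of depression".
- **Primary outcome.** Efficacy evaluations defines it as the MADRS from week 0 to week 16, with ten items each scored 0–6. Item 10 is therefore part of the outcome.
- **Assessor.** Under Blinding, "the researcher administering the outcome measurement will be unaware of the group assignment".
- **Analysis.** Data analysis states the intention-to-treat principle and a mixed-effect regression model.

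**The concern.** **Safety.** The sponsor treats an item-10 score above 4 as serious: it keeps a subject out of the trial and starts crisis care in weeks 1–4. At weeks 8 and 16 the trial collects the same score, and a self-injury questionnaire, in 12–17-year-olds who have left hospital. Nothing written obliges the assessor to pass the result on. The assessor is deliberately kept apart from treatment allocation, so a handover to the project doctors cannot be presumed.

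**Endpoint.** A check made to decide whether a subject may join a group session leads to withdrawal from the study. If staff apply those words literally, the scheduled MADRS visits of the most suicidal subjects may not take place. Primary-outcome data would then be missing because of a component of that outcome, and such missingness could differ between arms.

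**Working it through.** No figure in the Protocol measures this point directly, so the main check sets the rule against the schedule.

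**1. What the trigger means.** Item 10 runs from 0 to 6. With whole-number scores, above 4 means 5 or 6.

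**2. When the triggers operate.** Both are tied to treatment, and session 9 falls in week 4. Weeks without a trigger: 16 − 4 = 12 of 16.

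**3. Which scheduled MADRS visits have a later safety check.**

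| Visit | Later pre-session check? | Written action at the visit itself? |
| --- | --- | --- |
| Week 2 | Yes, ahead of session 5 | No |
| Week 4 | None if rated after session 9, which its description as the end of the intervention suggests | No |
| Week 8 | No | No |
| Week 16 | No | No |

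So 2 of the 4 post-baseline visits certainly have no later check, and 3 of 4 if week 4 is rated after the last session.

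**4. Whether other text fills the follow-up gap.** The Intervention section keeps conventional medication and care in place, which is treatment and not an alert route. The BAPT section mentions a risk-prevention scenario and reporting of adverse events to the Ethics Committee, but in the context of the games' physical safety. Neither says what follows a score of 5 or 6 at week 8 or 16.

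**5. What withdrawal could cost the endpoint.** Two post-baseline MADRS visits, weeks 2 and 4, fall in the session period. A subject withdrawn early who returns by week 8 could miss up to those two; later visits are at risk only if the subject does not return. The mixed model can normally use the remaining visits. That helps only in part, because the pre-session rating that triggers withdrawal is not itself a scheduled MADRS visit, so the model need not contain the score that caused the gap.

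**6. Whether power is the issue.** As an illustration only, take the sample-size inputs: difference 4.8, SD 9.5, two-sided α = 0.05, with the stated 90% read as power.

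- Reproducing the plan: n = 2(1.960 + 1.282)² × 9.5² / 4.8² gives 83 per arm by the normal formula. The t-test version gives 83.29, rounded up to the Protocol's 84.
- Power ≈ Φ(√(n/2) × 4.8/9.5 − 1.960). With 100 enrolled per arm and 16% ordinary loss, n = 84 and power is 90.6%.
- Assumed further loss of 5 points: n = 79, power 88.8%. Assumed further loss of 10 points: n = 74, power 86.7%.

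The Protocol gives no rate of item-10 scores above 4, and its 10%–20% loss allowance may already include such cases. Even under these assumptions the power cost is modest. The concern is which data would be missing, more than how many.

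**The case against.** The strongest reply concerns the endpoint half. The withdrawal is called temporary, so return is intended. Efficacy evaluations schedules both groups at every visit with no exception for paused subjects, and Data analysis states intention-to-treat. On this view the section has merely written study where it meant sessions. That largely stands: a pause in sessions is the likely intent. But intention-to-treat does not itself say that outcomes are collected after a safety withdrawal, and the follow-up visits in the safety section belong to crisis care by project doctors, not to blinded outcome rating.

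On the safety half, it can be said that the section only sets rules for group sessions with active games and is coherent for that purpose, and that silence about later visits is not a wrong statement. A separate risk document evidently exists, and the schedule and flow-chart figures cannot be seen here. This is fair as to the section's purpose. It remains that this is the Protocol's only written response to suicidality, and it stops while the trial goes on collecting the same score.

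A reader might infer more than the text supports:

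- **That outcome assessment stops for withdrawn subjects.** The Protocol does not say so; it is silent.
- **That all four post-baseline MADRS visits are lost.** This needs a withdrawal before week 2 that never ends, against the word temporary.
- **That discharged subjects are left without care.** Conventional medication and care continue.
- **That the rule will be applied differently across centres.** Recruitment is at one department of one hospital.

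**Conclusion.** The point holds in two limited parts. The follow-up gap is the firmer one: no action is written for an item-10 score above 4 at weeks 8 and 16, and both triggers are silent for 12 of 16 weeks. The endpoint part is a risk left open by wording: on a literal reading, week-2 and week-4 MADRS data, and later visits if the subject does not return, may be lost because of an item of the outcome.

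Neither the number of subjects affected nor the size or direction of any bias can be estimated, because no rate of such scores is given. The conclusion assumes that no document outside the Protocol already sets an alert route for the follow-up visits. Discontinuation rules and the response to a suicidality score belong in the protocol, so this is not something to leave to a statistical analysis plan. Label: cheap improvement.

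**What to change.** In Safety and monitoring, in both places where withdrawal is ordered, write instead: *suspended from group sessions until the project doctors judge it safe to return; the subject remains in the study and keeps all scheduled MADRS visits where clinically possible*.

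Then add: *An item-10 score above 4 at any scheduled MADRS visit (weeks 2, 4, 8 and 16), or severe self-injury or suicidal behaviour that becomes known at any time up to week 16, is reported to the project doctors by a one-way route that does not disclose allocation to the assessor, and starts the same crisis intervention and clinical follow-up.*

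The cost is the rewording of one section; every rating involved is already scheduled. There are downsides. Project doctors must be available through week 16. Some subjects in crisis will still miss visits. A crisis intervention at week 8 may affect week-16 scores in either arm.
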